#### Follow-up time points

2.6.3

Patient reported outcomes and radiographs will be obtained at six weeks, three and six-months post-surgery. Complications reported by the orthopaedic team will be documented by the research assistants from patient's medical records. The study timeline for participants recruitment and follow-up visits is described in Table 1 and Fig. 1.

**Table 1 tbl1:** Study timeline.

Assessment	Preoperative	Postoperative	2 weeks	6 weeks	3 months	6 months
**X-ray**	x			x	x	x
**CT-scan**	x					
**Participants screening**	x					
**Informed consent**	x					
**Participants eligibility**		x				
**Allocation**		x				
**Medical history**	x	x				
**Clinic visits (Complication outcomes)**			x	x	x	x
**Research visits (Functional outcomes)**				x	x	x

**Fig. 1 fig1:**
[figure not shown]
Flow chart showing participants enrolment and follow-ups during the study procedure.

### Recruitment procedure

2.7

The research administrator ([name]) at the centre will make the first approach for screening and explaining the study to potential participants. Eligible participants who are interested in our study will be provided with the information sheet and encouraged to consult with their GPs, family and friends about the study. They will be given adequate time to consider participating in the study prior to their operation. Informed consent for study participation will be obtained prior to surgery. Retrospective data collected from Christchurch Hospital theatre records showed 291 ankle fractures (excluding those with syndesmosis fixation) were operated on during a 12-month period. On the assumption that 50% of these patients would meet the inclusion criteria and agree to participate in our study, we estimate completing recruitment within one year.

### Randomisation

2.8

A statistician who is not involved in the study will prepare a computer-generated random sequence using blocks of 4 with a 1 to 1 ratio, IWB and DWB groups. At the completion of the operation, and once the stability of fixation is confirmed by the operating surgeon, the research administrator who is independent of the treatment will perform the randomisation using concealed sequentially numbered, opaque and sealed envelopes and will inform the research team of patient allocation group.

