**Method:**

32 adult participants with unimalleolar, bimalleolar or trimalleolar ankle fractures and stable fixation following ankle ORIF will be randomly allocated to either Immediate Weight Bearing (IWB) or Delayed Weight Bearing (DWB) groups. Stability of fixation is a subjective assessment made by the operating surgeon at the completion of fixation and is independent of fracture pattern. Participants in the IWB group will be allowed to weight bear as tolerated within 24 h, while participants in the DWB group will remain non-weight bearing for six weeks. Participants’ data including Olerud and Molander Ankle Score, Self-Reported Foot and Ankle Score, SF-36 health survey, time to return to work will be collected. X-rays will be assessed by orthopaedic team members for fixation-related complications including reduction loss, malreduction/malunion, implant failure and non-union. Participants data will be collected at six weeks, three and six-months post-surgery. We will determine the feasibility of a full RCT through assessing the recruitment rate, adherence rate, and drop-out rate.

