### Study design

2.1

We will conduct a parallel group, superiority designed, and open label pilot RCT, and randomise participants with ankle fracture and open reduction internal fixation to either immediate weight bearing (IWB) or delayed weight bearing (DWB) group post-surgery.

This study will be reported following Standard Protocol Items: Recommendation for interventional trial statement (SPIRIT) [18]. The study will be performed according to the Declaration of Helsinki. This trial has been registered with the Australian New Zealand Clinical Trials Registry (ANZCTR): ACTRN12623001107617. Ethical approval was obtained from Health and Disability Ethics Committees (HDECs). Informed consent will be obtained from all patients, informing them of the study aims, procedures and possible risks.

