### Study setting

2.2

Participants will be recruited between February to December 2024 from Christchurch Hospital, a tertiary trauma centre in Christchurch, New Zealand. We anticipate the full RCT running at this centre, in addition to other secondary and tertiary hospitals in New Zealand.

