### Blinding

2.9

Due to the nature of the study, surgeons and patients will be unblinded to the group allocation. A research assistant who records the patient clinical outcomes including function and quality of life questionnaires will also be unblinded to the group allocation. Patients' reported questionnaires (objective outcome measures) will not carry the risk of reporting bias, and the blinding status of assessors is unlikely to affect patients’ reporting [30]. Other outcome measures (e.g. time to return to work, time to full weight bearing and post-operative complications) will be collected by unblinded research team members from the patient reporting log, and the wider orthopaedic team, who are involved with patient treatment, but not directly involved with the study. It is possible that those treating team members may carry bias if they are aware of the treatment arm, particularly in the reporting of complications.

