### Sample size

2.10

The minimum clinically important difference for the OMAS was reported 10.5 at three months [24]. Considering the average standard deviation at 16 from prior studies, this gives a sample size of 50 per group for the main trial to achieve 90 % power at a two-sided alpha of 0.05. Given a 20 % drop-out, we will need 120 participants in total for the full trial. In order to minimise the sample size of the pilot and main trial combined, and considering the medium effect size of 0.66, it is recommended that 13 participants per group are recruited for the pilot study [31]. Given a drop-out rate of 20 %, we will need a total of 32 participants for the pilot trial. It is anticipated that these patients will carry over to participate in the ongoing full RCT, pending a successful pilot RCT, ethics approval and appropriate funding.

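### A single published block size of 4, with a subjective eligibility call just before the envelope, lets anyone who follows the sequence foresee a third of allocations

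*Protocol article*

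**What the plan says.** Section 2.8 (Randomisation) has an uninvolved statistician prepare a "computer-generated random sequence using blocks of 4 with a 1 to 1 ratio". No second block size and no stratification factor is described. The research administrator, who is independent of treatment, opens opaque, sealed, numbered envelopes after the operation, "once the stability of fixation is confirmed by the operating surgeon", and then tells the research team the result.

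The setting makes past allocations visible. Section 2.1 describes a "parallel group, superiority designed, and open label pilot RCT". Section 2.2 recruits "from Christchurch Hospital, a tertiary trauma centre in Christchurch, New Zealand". Section 2.9 states that "surgeons and patients will be unblinded to the group allocation".

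The abstract says of the final eligibility step: "Stability of fixation is a subjective assessment made by the operating surgeon at the completion of fixation". Section 2.3 makes questionable stability, as judged by that surgeon, a reason for exclusion.

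The pilot size is given in section 2.10: "we will need a total of 32 participants for the pilot trial". The same section expects these patients to continue into the full RCT, subject to a successful pilot, ethics approval and funding.

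**The concern.** Sealed envelopes hide the next assignment physically. They do not stop someone from working it out when every block has the same known size and the earlier assignments are known. This article itself publishes the size.

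Predictability matters here because a discretionary decision comes immediately before the envelope. If the person judging a borderline fixation expected a particular arm, that expectation could influence whether the patient is declared eligible. The Introduction notes that some surgeons avoid early weight bearing because they fear displacement, so a motive is at least plausible.

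Three products of the pilot are exposed:
- the proportion enrolled out of those screened, which is part of a primary outcome (section 2.6.1);
- the data on patients excluded for unsuitable fixation, which are meant to inform selection in the full RCT (section 2.5);
- the clinical data that may carry over to the full RCT (section 2.10).

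**Working it through.** **Inputs.** Block size 4, ratio 1:1 (section 2.8). Pilot size 32 (section 2.10). The protocol gives no figure for predictability, so there is none to reproduce. Its 32 follows from its own inputs: 13 per group × 1.2 = 15.6, rounded up to 16, and 2 × 16 = 32. That is 32 / 4 = 8 complete blocks.

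**Certain allocations.** A 1:1 block of 4 has 6 equally likely orders. An allocation is certain once one arm has used both its places.
- Positions 1 and 2: never certain.
- Position 3: certain when the first two match, probability 1/3.
- Position 4: always certain.

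Expected per block: 1/3 + 1 = 1.333. As a share: 1.333 / 4 = 33.3%. Over 8 blocks: 8 × 1.333 = 10.7 of 32.

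**Best guess.** Always guess the arm with more places left in the block.
- Position 1: 1/2.
- Position 2: 2/3.
- Position 3: (1/3 × 1) + (2/3 × 1/2) = 2/3.
- Position 4: 1.

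Sum: 0.500 + 0.667 + 0.667 + 1 = 2.833. As a share: 2.833 / 4 = 70.8%, or 22.7 of 32, against 50% with no information.

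**Alternatives.** Fixed sizes are enumerated exactly. Mixed sizes come from 4,000 simulated sequences of 32 with the sizes equally likely. The guesser in the simulation makes the best use of all past allocations and knows which sizes are in use, but not their order. The same simulation with a fixed block of 4 returns 33.4% and 70.9%, in agreement with the exact values.

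| Scheme | Certain in advance | Of 32 | Best guess right |
|---|---|---|---|
| Fixed 4 (plan) | 33.3% | 10.7 | 70.8% |
| Fixed 6 | 25.0% | 8.0 | 68.3% |
| Fixed 8 | 20.0% | 6.4 | 66.6% |
| Random 2/4/6 | 3.9% | 1.2 | 69.9% |
| Random 4/6 | 5.6% | 1.8 | 68.8% |
| Random 4/6/8 | 2.4% | 0.8 | 67.6% |

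Varying the size removes most of the certainty but little of the advantage in guessing. Including blocks of 2 keeps the guessing rate close to 70%.

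**The case against.** The strongest objection is that the 33% is conditional. It applies to someone who knows the block size and has every earlier allocation in order. Section 2.4 has registrars, fellows and consultants operating, and section 2.9 describes the wider orthopaedic team as not directly involved in the study. Unblinding of surgeons need mean no more than knowing the arm of their own patients, and nothing says that an operating surgeon sees the running sequence. This stands: about 11 of 32 is the figure for a full-sequence observer, not for each surgeon.

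A reader might also infer that the administrator, who both approaches patients and opens envelopes, could steer entry. The documents do not support that. Consent precedes surgery, the administrator is independent of treatment, and the stability call belongs to the surgeon. The person best placed to predict does not make the subjective decision.

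A further tempting reading is that firmer fixations would end up in the immediate weight-bearing arm and flatter it. That is conceivable, but the documents establish neither its direction nor its size.

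The safeguards are real: an outside statistician, concealed envelopes, consent before surgery, and data kept on patients excluded for unsuitable fixation. The last helps to detect selection. None of them prevents deduction from past allocations.

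Finally, the pilot's primary outcomes are feasibility measures and section 3 plans only descriptive reporting. This limits the immediate damage. It does not remove the exposure of the enrolled/screened proportion or of data carried forward.

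**Conclusion.** The vulnerability is real but conditional, and it is cheap to reduce. With a fixed, published block of 4 at one open-label site, an observer of the full sequence is certain of 33.3% of allocations (10.7 of 32) and guesses correctly 70.8% of the time. A discretionary exclusion step sits directly before randomisation.

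This rests on three assumptions: one unstratified list, as described; knowledge of the block size; and sight of all earlier allocations in order. The last is feasible for the research team, which is told each allocation, and is not shown for individual surgeons.

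Selective exclusion is therefore possible, not demonstrated. The documents do not support a claim that the pilot is biased in a given direction, or that its feasibility results are invalid.

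**What to change.** For allocations not yet made, and for the full RCT, have the independent statistician generate a list with randomly varying block sizes that omits blocks of 2, for example 4, 6 and 8. Neither the sizes nor their order should be disclosed to site staff or surgeons. The published size of 4 cannot be withdrawn, so concealment can apply only to a new list.

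As a supporting step, record the surgeon's stability decision with a time before the envelope is taken. Section 2.8 already sets that order. The record makes exclusions auditable but cannot stop a surgeon from anticipating an arm.

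The cost is one new list and one logged field. The statistical downside is a possible imbalance if recruitment stops mid-block: at most half the largest block, so 8 / 2 = 4 participants, against 4 / 2 = 2 under the present scheme.

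### The research administrator both recruits patients and opens the allocation envelopes, so with fixed blocks of 4 the recruiter can often predict the next allocation

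*Protocol article*

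**What the plan says.** Recruitment procedure (2.7) says that the research administrator at the centre "will make the first approach for screening and explaining the study to potential participants". Consent comes later but still before the operation: "Informed consent for study participation will be obtained prior to surgery". The section does not say who takes consent. Ethics and disclosures only rules out the main investigator.

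Randomisation (2.8) has an uninvolved statistician prepare a "computer-generated random sequence using blocks of 4 with a 1 to 1 ratio". The trigger for allocation is given as "At the completion of the operation, and once the stability of fixation is confirmed by the operating surgeon". At that point "the research administrator who is independent of the treatment will perform the randomisation using concealed sequentially numbered, opaque and sealed envelopes", and the same person "will inform the research team of patient allocation group".

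Study setting (2.2) gives a single hospital. Blinding (2.9) makes surgeons, patients and the research assistant who records outcomes aware of the arm.

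**The concern.** Allocation concealment protects a trial against anyone who influences entry knowing, or being able to guess, the next assignment. The independence that counts is therefore independence from recruitment. The protocol offers independence from treatment instead, and gives recruitment and randomisation to the same role.

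This is a stated rule, not a detail left to a fuller document. Anyone who follows it will open each envelope, learn the arm, and then approach the next patient knowing the run of allocations so far. If the next arm can be guessed, the vigour of the approach or the slant of the explanation can shift with it, even without intent. The arms could then differ before treatment starts. In an open-label trial with unblinded outcome collection, sound allocation is one of the few protections against bias still available.

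**Working it through.** The protocol gives no figure on this point, so there is none to reproduce. The check has two parts: who does what, and how predictable the sequence is to someone who sees past allocations.

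**Who does what, in order**

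| Step | When | Who | Section |
|---|---|---|---|
| Sequence prepared | Before recruitment (implied) | Uninvolved statistician | 2.8 |
| Screening, first approach, explanation | Before surgery | Research administrator | 2.7 |
| Consent | Before surgery | Not named; not the main investigator | 2.7; Ethics and disclosures |
| Stability decision | End of surgery | Operating surgeon | 2.8 |
| Randomisation by envelope | After the stability decision | Research administrator | 2.8 |
| Allocation announced | After randomisation | Research administrator | 2.8 |

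Both sections use the same role title with the definite article. No other person or central service is described as releasing allocations. For any one patient, the approach comes before that patient's envelope is opened. For the next patient, the approach comes after all earlier envelopes have been opened by the person approaching.

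**How predictable the next allocation is**

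Inputs: block size 4, ratio 1:1 (2.8); no stratification mentioned; 32 participants (2.10), so 32 / 4 = 8 blocks. Assumptions: the recruiter knows all past allocations and the block size, and the patient approached is the next one randomised.

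A 1:1 block of 4 has 6 equally likely arrangements: AABB, ABAB, ABBA, BAAB, BABA, BBAA.

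*Allocations fully determined by earlier ones in the block.* The fourth is always determined. The third is determined as well when the first two match (AABB, BBAA).
- Mean per block = (2 + 1 + 1 + 1 + 1 + 2) / 6 = 8 / 6 = 1.33.
- As a share: 1.33 / 4 = 33.3%.
- Over 8 blocks: 8 × 1.33 = 10.7 of 32.

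*Best guess, always naming the arm with more places left in the block.*
- First place: 1/2.
- Second place: 2/3.
- Third place: (1/3 × 1) + (2/3 × 1/2) = 2/3.
- Fourth place: 1.
- Sum = 0.500 + 0.667 + 0.667 + 1.000 = 2.833 per block, or 2.833 / 4 = 70.8%.
- Over 8 blocks: 8 × 2.833 = 22.7 of 32, against 16 of 32 by chance.

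The same enumeration for larger fixed blocks gives 25% determined and 68.3% guessed correctly for blocks of 6, and 20% and 66.6% for blocks of 8. A larger fixed block alone helps only a little.

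These figures measure predictability, not bias. Turning them into a bias would need the strength of any selective approach and the prognosis of the patients affected, and the protocol gives neither.

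**The case against.** The strongest reply is that the protocol already has several real safeguards. The sequence comes from someone outside the study, and the envelopes are numbered, opaque and sealed. Consent precedes surgery, and the final eligibility decision belongs to the surgeon, before the envelope is opened. All of this stands. It limits manipulation of the current patient's allocation, but it does not reach the earlier step of approach and explanation.

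A reader might infer that the administrator keeps the envelopes, can get at the next one, or has discretion over whom to approach. The text supports none of these. It says who performs the randomisation, not where envelopes are stored, and it assigns the first approach without granting any choice of patients. Nor does it follow that envelope concealment has failed.

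Other replies carry weight:

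- **Overlap with block size.** Knowing past allocations helps only if the sequence is predictable, and the fixed block of 4 is what makes it so. The two features work together and should be fixed together.
- **Timing.** Which envelope a patient reaches depends on theatre order and on who passes the stability decision, so the 71% is an upper figure when several patients are waiting at once. At the feasibility threshold of two participants a month (Statistical analysis) such overlap would be uncommon.
- **Screening log.** Section 2.6.1 reports enrolled over screened, which may help reveal selective enrolment, but only after the event.
- **Limited stakes in the pilot.** The primary outcomes are recruitment, adherence and drop-out, and the arm data are to be summarised descriptively. Carry-over to the full trial is conditional on success, ethics approval and funding.
- **Partial remedy.** In an open-label, single-centre trial a recruiter could learn allocations without opening envelopes. This is true, and it is why separating the roles is not enough alone.

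**Conclusion.** The point holds in limited form. One role recruits, randomises and announces, and the independence stated is of the wrong kind. If the block size is known and patients are randomised in the order approached, about one third of allocations (10.7 of 32) are predictable with certainty and about 71% (22.7 of 32) by best guess. The route is prediction that influences approach or explanation, not sight of a sealed envelope.

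The size of any resulting bias cannot be computed from the protocol. The feasibility outcomes are little affected. The exposure lies in the short-term comparison of arms named in the Aim and in the full RCT if these patients carry over: 32 of the planned 120 is 32 / 120 = 26.7% of that sample, and selection built in now could not be removed later. This is a worthwhile, cheap improvement and not a defect that invalidates the pilot.

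**What to change.** Amend section 2.8 so that:

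1. Allocation is released by existing staff who take no part in screening, approach or consent, or by a web randomisation module. Using the statistician who prepares the sequence would end that person's stated non-involvement, so another releaser is cleaner.
2. Release happens only after consent and the surgeon's stability decision have both been logged.
3. The recruiter is not given the cumulative allocation list while recruitment is open.
4. Block sizes vary and are not disclosed to the trial team or in public documents while recruitment is open. This is needed alongside items 1 to 3, because separating the roles does not stop a recruiter learning past allocations informally.

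If the roles are already separate in practice, one sentence in 2.8 saying so would cover items 1 and 2.

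The cost is a wording amendment and a small change of procedure, with no extra patients, visits or analyses. The one practical burden is that a person or system must be available whenever an eligible operation ends. A pilot is a good place to test that, before the procedure is taken to other hospitals.

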### Blinding

2.9

Due to the nature of the study, surgeons and patients will be unblinded to the group allocation. A research assistant who records the patient clinical outcomes including function and quality of life questionnaires will also be unblinded to the group allocation. Patients' reported questionnaires (objective outcome measures) will not carry the risk of reporting bias, and the blinding status of assessors is unlikely to affect patients’ reporting [30]. Other outcome measures (e.g. time to return to work, time to full weight bearing and post-operative complications) will be collected by unblinded research team members from the patient reporting log, and the wider orthopaedic team, who are involved with patient treatment, but not directly involved with the study. It is possible that those treating team members may carry bias if they are aware of the treatment arm, particularly in the reporting of complications.

### Sample size

2.10

The minimum clinically important difference for the OMAS was reported 10.5 at three months [24]. Considering the average standard deviation at 16 from prior studies, this gives a sample size of 50 per group for the main trial to achieve 90 % power at a two-sided alpha of 0.05. Given a 20 % drop-out, we will need 120 participants in total for the full trial. In order to minimise the sample size of the pilot and main trial combined, and considering the medium effect size of 0.66, it is recommended that 13 participants per group are recruited for the pilot study [31]. Given a drop-out rate of 20 %, we will need a total of 32 participants for the pilot trial. It is anticipated that these patients will carry over to participate in the ongoing full RCT, pending a successful pilot RCT, ethics approval and appropriate funding.

